**Figure 1 figure1:**
[figure not shown]
In-game user interface of the Move Sapiens virtual reality exergame (active intervention group): (A) active combat scenario with explosion and (B) environmental view.

#### Control Condition (Nonexercise VR)

Participants assigned to the control group will use an adapted nonexercise version of Move Sapiens. This version preserves the same immersive VR environment, visual assets, and sound design but removes all components of physical exertion. Interaction occurs exclusively through a joystick. Session duration and frequency mirror those of the intervention group. This design enables examination of the specific contribution of vigorous physical exertion to the observed outcomes while controlling for VR immersion and digital engagement, both of which are preserved across conditions.

#### Game Design Framework

The development of Move Sapiens followed current guidelines for serious games in ADHD, particularly the IDEAL-Games framework [12], which structures development into sequential stages (idea, development, exploration, assessment of effectiveness, and long-term follow-up) and emphasizes user-centered, theory-driven design. In line with these recommendations, the game was created by a multidisciplinary team (psychiatry, exercise science, and game design), and its mechanics explicitly operationalize core cognitive targets (sustained attention, inhibitory control, and planning) through short, discrete tasks with adaptive difficulty, clear feedback, and limited session length. Reward schedules, audiovisual “juiciness,” and time constraints were planned to maximize engagement while minimizing the risk of problematic use or gaming addiction, as suggested for ADHD-oriented serious games.

### Procedures

The intervention follows a structured 5-week timeline comprising recruitment, laboratory adaptation, and home-based training. The workflow is divided into 4 distinct phases (Figure 2).

**Figure 2 figure2:**
[figure not shown]
Study design flowchart and participant timeline. GEQ: Game Experience Questionnaire; HIIT: high-intensity interval training; PACES: Physical Activity Enjoyment Scale; SSQ: Simulator Sickness Questionnaire; VR: virtual reality.

#### Phase 1: Recruitment and Baseline (Weeks 0 to 1)

Potential participants undergo an initial online screening. After provision of informed consent, a comprehensive psychiatric evaluation is conducted by 2 child and adolescent psychiatrists to confirm eligibility, establish the ADHD diagnosis, and screen for psychiatric comorbidities using the Schedule for Affective Disorders and Schizophrenia for School-Aged Children [13]. Eligible adolescents then proceed to the first in-person visit (visit 1), which includes the complete baseline neuropsychological assessment, physiological baseline recording (heart rate), and self-report questionnaires (Pittsburgh Sleep Quality Index and 7-item Generalized Anxiety Disorder scale). Additionally, participants experience their first exposure to the VR environment (habituation) to assess tolerability and equipment fit without engaging in the intervention protocol.

#### Phase 2: Familiarization and Safety (Week 1)

Following baseline, participants complete 3 consecutive days of supervised familiarization (visits 2 to 4) in the research center. In these sessions, participants learn to operate the Meta Quest 2 and 3S headsets and practice the specific game version corresponding to their allocation (HIIT VR or control VR). During these sessions, the research staff continuously monitors safety parameters, including heart rate (via Polar H10 sensors) and potential cybersickness symptoms. The final familiarization session includes a review of the participants’ daily routine to establish the optimal time for home practice and signing of the equipment responsibility form.

#### Phase 3: Home-Based Intervention (Weeks 2 to 5)

Participants take the VR headset home for a 4-week period. The protocol requires 1 session per day, 5 days per week (20 sessions in total). Adherence is strictly monitored via WhatsApp. Immediately after each session, participants must send (1) a screenshot of their final game score and (2) their rating on the Borg scale of perceived exertion (6 to 20). We enforce strict adherence to ensure intervention fidelity. Participants who miss a scheduled weekday session are required to make up the missed training on the weekend to maintain the total weekly dose. Three unjustified absences or failure to complete the required number of sessions despite makeup opportunities will result in exclusion from the study.

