#### Eligibility Criteria

We will include participants aged 12 to 17 years with a confirmed diagnosis of ADHD according to the Diagnostic and Statistical Manual of Mental Disorders, Fifth Edition. Additionally, participants must demonstrate a score of 12 or higher on the Swanson, Nolan, and Pelham Rating Scale version IV inattention subscale. Regarding medication status, we will include participants who are either medication naive or not currently using ADHD medication (having discontinued use prior to study enrollment for at least 30 days). Importantly, the study does not request or encourage the discontinuation of prescribed medication for research purposes. However, participants who initiate or resume pharmacological treatment during the study period for clinical reasons will be withdrawn from the study to avoid confounding effects.

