#### Phase 4: After the Intervention (Week 5)

Upon completion of the 20 sessions, participants return for the final visit (visit 5). Neuropsychological and behavioral assessments identical to those at baseline are readministered, and the VR equipment is returned.

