### Outcomes

#### Overview

We will assess outcomes at baseline (visit 1) and the postintervention time point (visit 5). The specific measures are categorized as follows (Table 1).

**Table 1 table1:** Summary of outcome measures.

Outcome domain			Instrument		Metric

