### Statistical Methods

All participants will be included in an intention-to-treat analysis. Continuous outcomes will be examined using linear mixed-effects models with random intercepts accounting for repeated measures and missing data. The models will include terms for treatment group, time (modeled as a continuous variable), and the treatment-by-time interaction to estimate differential change between groups. An autoregressive covariance structure will be applied to account for temporal correlation. Statistical significance will be defined as a 2-sided *P* value of less than .05. Between-group effect sizes will be estimated using the Cohen *d*. All analyses will be conducted using RStudio (Posit PBC).

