### Data Management and Safety Monitoring

The REDCap (Research Electronic Data Capture; Vanderbilt University) platform will be used for data management. To ensure integrity and blinding, the blinded team enters assessment data into a restricted partition, whereas the unblinded team logs adherence and physiological data separately. All manual entries from paper forms undergo a double-check verification process by a supervisor. Data are stored on secure servers with regular backups, and the final dataset will remain locked until the analysis plan is finalized.

Regarding safety monitoring, given the low-risk nature of the exergame intervention, a formal external data monitoring committee was not convened. Instead, continuous monitoring for cybersickness and physical discomfort is conducted by the unblinded team supervisors and reviewed weekly by the steering committee. Participants reporting persistent adverse effects are withdrawn according to established safety protocols.

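### Randomised participants are removed from the study for non-adherence, medication start or adverse effects, which undermines the promised intention-to-treat analysis of all participants

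*Protocol article*

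**What the plan says.** The analysis promise, in Statistical Methods, is unqualified: "All participants will be included in an intention-to-treat analysis". The same section relies on the model for missing values: "Continuous outcomes will be examined using linear mixed-effects models with random intercepts accounting for repeated measures and missing data".

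Three conduct rules remove people:

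- Procedures, Phase 3: "Three unjustified absences or failure to complete the required number of sessions despite makeup opportunities will result in exclusion from the study".
- Eligibility Criteria: "participants who initiate or resume pharmacological treatment during the study period for clinical reasons will be withdrawn from the study to avoid confounding effects".
- Data Management and Safety Monitoring: "Participants reporting persistent adverse effects are withdrawn according to established safety protocols".

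The first two name the study, not the training, as what the participant leaves. The third does not say which is meant.

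Allocation is already in use in week 1, when participants "practice the specific game version corresponding to their allocation (HIIT VR or control VR"), and the session rule operates in weeks 2 to 5. On measurement, the Outcomes overview says "We will assess outcomes at baseline (visit 1) and the postintervention time point (visit 5"), and Phase 4 describes that last visit only for those who finish: "Upon completion of the 20 sessions, participants return for the final visit (visit 5"). The article nowhere says that excluded or withdrawn participants are still assessed.

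**The concern.** An intention-to-treat comparison keeps the groups as randomised. Here retention depends on what participants do, or what happens to them, after randomisation. With one post-baseline assessment, a participant removed before visit 5 has no outcome on either primary measure, and a mixed model cannot recover it.

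There are reasons to doubt that such losses are explained by baseline. The task to be completed differs by arm: intervals of maximal effort against joystick play. The Abstract links the exertion and repetitiveness of traditional HIIT to poor adherence in ADHD. Medication started for clinical reasons may reflect symptoms during follow-up, which the baseline score does not capture.

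At stake is whether the estimate describes the adolescents who were randomised or mainly those who completed 20 sessions without medication. Bias could go either way. Losing poor adherers from the HIIT arm could flatter HIIT, while losing unimproved controls who start medication could flatter control.

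**Working it through.** **1. Who lacks an outcome.** The Sample Size section expects 30% attrition from 98. That leaves 98 × 0.70 = 68.6 with a visit 5, about 34 per arm. Results gives 46 of 58 completed, 46/58 = 79.3%. The other 58 − 46 = 12 (20.7%) may include participants still in training.

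**2. What the mixed model gains from baseline-only participants.** Simulation with no true effect, 49 per arm, 30% attrition overall and an assumed baseline-to-post correlation of 0.5, 250 runs per scenario. The random-intercept model with a group-by-time term was fitted to everyone and then to completers only. The standard error of the interaction was about 0.23 against 0.24, and the two estimates correlated 0.94 to 0.96. Participants with only a baseline barely move the result.

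**3. Raw completer difference (illustration).** Bias = (gap between removed and retained) × (difference in removal proportion). With an assumed gap of 0.5 SD and assumed removal of 30% against 10%: 0.5 × (0.30 − 0.10) = 0.10 SD. Gaps of 0.3 and 0.8 SD give 0.06 and 0.16 SD. This is the bias of an unadjusted completer comparison, not of the planned model.

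**4. When baseline is taken into account.** Only the part of the gap not explained by baseline remains.

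- Removal driven by baseline severity, 30% against 10%, gap about 0.5 SD, correlation 0.5: the raw completer difference is biased by about 0.09 SD, the baseline-adjusted estimate by about 0.00.
- Removal related to the post-intervention score (mixed model on everyone minus the full-data estimate, from the simulation in step 2). Type I error is from a related baseline-adjusted completer analysis at nominal 0.05:

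| Removal, arm 1 / arm 2 | Correlation of removal with post score, arm 1 / arm 2 | Bias in mixed model (SD) | Type I error |
|---|---|---|---|
| 40% / 20% | 0.3 / 0.3 | −0.084 − (−0.022) = −0.06 | 0.066 |
| 40% / 20% | 0.5 / 0.5 | −0.128 − (−0.016) = −0.11 | 0.087 |
| 30% / 30% | 0.5 / 0 | −0.190 − (−0.005) = −0.19 | 0.146 |

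The sign follows from which arm was given the heavier or more selective loss, so it says nothing about the direction in this trial. In the last row the dropout counts are equal, so equal counts alone would not be reassuring.

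**5. Power (two-sided t-test, α = 0.05).**

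- 34 per arm, d = 0.50: 0.53.
- 49 per arm, d = 0.50 (no dilution): 0.69.
- 49 per arm, with the recovered 30% gaining nothing, d = 0.70 × 0.50 = 0.35: 0.40.

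Power at 49 per arm equals 0.53 when d is about 0.415. Solving 0.35 + 0.15k = 0.415 gives k ≈ 0.43, so the recovered participants must keep about 43% of the effect for power to gain. These figures also treat all 30% as recoverable, although the plan does not split attrition by cause.

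**The case against.** Several points on the other side stand.

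- The planned model is likelihood-based and includes baseline, so missingness explained by baseline severity is handled. The 0.10 SD in step 3 therefore overstates what that mechanism alone would do to the planned analysis.
- A reader might infer that missingness is known to differ by arm. The document does not show this. The rules are the same in both arms, attrition by arm is not reported, the adherence remark concerns traditional HIIT, and the pilot of this game reported high motivation and enjoyment. The 30%/10% split is invented and averages 20%, not the planned 30%.
- A reader might infer that any missed session removes a participant. It does not: weekend makeup comes first, and the rule then needs three unjustified absences or an unmet session total.
- A reader might infer that following everyone up raises power from 0.53 to 0.69. That holds only without dilution.
- The Phase 4 sentence describes the path of completers and does not itself rule out assessing others. A full protocol could provide for follow-up after discontinuation.
- The Discussion states the aim of isolating the exercise effect from medication, so a hypothetical strategy for medication start is a legitimate choice.

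None of this removes the conflict. Leaving the study is the article's own wording for two of the rules, and an analysis plan cannot supply outcomes that those rules stop being collected.

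**Conclusion.** The conduct rules and the analysis promise contradict each other and must be reconciled. Followed as written, the analysis is intention-to-treat in name. It is not literally restricted to completers, because baselines stay in the model, but it behaves much like a completers' analysis that is valid only if loss is random given baseline.

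Confidence is high in the contradiction and low in the size of the bias. Under the assumed removal rates and correlations, bias runs from near 0 (removal depends on baseline only) to roughly 0.06 to 0.19 SD (removal depends on the post score), against a planned effect of 0.50. Direction is unknown, and dependence on arm is a reasonable inference rather than a documented fact. The issue touches both primary outcomes. It should be settled while collection continues, to October 2026 on the stated timeline, with up to 98 − 58 = 40 participants still to enrol as of April 2026.

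**What to change.** Reconcile Eligibility Criteria, Phase 3, Phase 4 and Safety Monitoring with Statistical Methods by separating stopping the training from leaving the study.

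- Invite every randomised participant to visit 5 in a fixed window counted from randomisation, whatever sessions were completed or medication started. If the visit is refused, collect the parent-reported SNAP-IV remotely.
- Put all collected data, by randomised arm, into the primary intention-to-treat analysis. Treat per-protocol and hypothetical (no medication) analyses as supportive. If the sponsor prefers a hypothetical strategy for medication start, state it and still collect the data.
- For participants already excluded, seek the outcome where the window allows.
- Report numbers and reasons for removal by arm.

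The rules on stopping training, on medication and on safety withdrawal are left as they are; only outcome follow-up changes.

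Cost: an amendment and some extra follow-up at a visit that already exists. The effect estimate may be diluted by non-adherence, with the possible loss of power shown above. Mainly participants not yet through the trial would benefit.

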#### Phase 4: After the Intervention (Week 5)

Upon completion of the 20 sessions, participants return for the final visit (visit 5). Neuropsychological and behavioral assessments identical to those at baseline are readministered, and the VR equipment is returned.

### Outcomes

#### Overview

We will assess outcomes at baseline (visit 1) and the postintervention time point (visit 5). The specific measures are categorized as follows (Table 1).

**Table 1 table1:** Summary of outcome measures.

Outcome domain			Instrument		Metric
**Primary**					
	Inattention symptoms	SNAP-IV^a^ inattention subscale (parent report)		Change (Δ) in total inattention score (range 0-27)	
	Inhibitory control	Go/no-go task (computerized)		Number of commission errors (responses to “no-go” stimuli); age corrected	
**Secondary**					
	Verbal working memory	Digit span task (backward condition)		Scaled score for the backward condition	
	Spatial working memory	Spatial span task (Corsi block paradigm)		Number of correct responses in the backward condition; age corrected	
	Cognitive flexibility	Trail making test (part B)		Completion time; age adjusted	
	Processing speed	2-choice reaction time task		Average reaction time for correct responses; age corrected	
	Impulsivity	MOXO-CPT^b^		Impulsivity *z*-score (standardized)	
	Sleep quality	PSQI^c^		Change (Δ) in global score (range 0-21)	
	Anxiety symptoms	GAD-7^d^		Change (Δ) in total score	
**Other prespecified domains**					
	Physiological exercise intensity	Polar H10 HR^e^ monitor (processed using the Kubios software)		Average HR, HR_max_^f^, HRR^g^ (Δ in bpm^h^ over 5 min), and HRV^i^ indexes	
	Game experience	GEQ^j^		Subscale scores and/or total experience score	
	VR discomfort	SSQ^k^		Incidence or severity of nausea, oculomotor issues, and disorientation	
	Enjoyment	PACES^l^		Total enjoyment score	

^a^SNAP-IV: Swanson, Nolan, and Pelham Rating Scale version IV.

^b^MOXO-CPT: MOXO continuous performance test.

^c^PSQI: Pittsburgh Sleep Quality Index.

^d^GAD-7: 7-item Generalized Anxiety Disorder scale.

^e^HR: heart rate.

^f^HR_max_: maximum heart rate.

^g^HRR: heart rate reserve.

^h^bpm: beats per minute.

^i^HRV: HR variability.

^j^GEQ: Game Experience Questionnaire.

^k^SSQ: Simulator Sickness Questionnaire.

^l^PACES: Physical Activity Enjoyment Scale.

#### Primary Outcomes

Primary outcomes comprise (1) inattention symptoms (assessed via the Swanson, Nolan, and Pelham Rating Scale version IV inattention subscale [parent report]), for which the primary metric is the change in the total inattention score [14]; and (2) inhibitory control (measured via a computerized go/no-go task [15]), for which the primary metric is the number of commission errors (responses to “no-go” stimuli), representing a failure in inhibitory control.

#### Secondary Outcomes

Secondary outcomes comprise (1) impulsivity (evaluated using the MOXO continuous performance test), for which the primary metric of interest is the standardized impulsivity *z*-score assessing the inhibition of impulsive responses under varying levels of environmental distractors; (2) verbal working memory (assessed using the digit span task [forward and backward conditions] to measure phonological loop capacity [16]); (3) spatial working memory (measured via the spatial span task [forward and backward conditions] assessing the ability to retain and manipulate visuospatial information [17]); (4) cognitive flexibility (evaluated using the trail making test; while both parts are administered, the outcome measure for executive shifting is the time to completion of part B [age corrected] [18]); (5) processing speed (measured using the 2-choice reaction time task analyzing both the mean reaction time and response variance [19]); (6) sleep quality (assessed via the Pittsburgh Sleep Quality Index, where a global score greater than 5 indicates significant sleep difficulties [20]); and (7) anxiety symptoms (measured using the 7-item Generalized Anxiety Disorder scale to monitor changes in anxiety levels throughout the intervention [21]).

#### Additional Measures

Additional measures comprise, first, physiological load and perceived exertion. Heart rate is monitored continuously during laboratory sessions using Polar H10 sensors. Additionally, we collect the Borg rating of perceived exertion (6 to 20) after every session (laboratory and home) to quantify training intensity [22].

The second additional measure is user experience and tolerability. VR-specific effects are assessed after exposure using the Simulator Sickness Questionnaire for adverse effects [23], the Physical Activity Enjoyment Scale for engagement [24], and the Game Experience Questionnaire for usability [25].

### Sample Size

The sample size calculation assumed a statistical power of 0.80, a significance level of an α value of .05, and a medium effect size of 0.50, consistent with literature on exercise interventions in ADHD. Accounting for an expected attrition rate of 30%, the required total sample size is 98 participants, with 49 participants allocated to each study arm. We will balance recruitment across the 2 study sites.

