## Introduction

Attention-deficit/hyperactivity disorder (ADHD) is a prevalent neurodevelopmental condition that affects approximately 7% of children and adolescents worldwide and is associated with substantial academic, social, and functional impairment that often persists into adulthood [1,2]. Pharmacotherapy, particularly psychostimulants, remains a mainstay of treatment and is effective in reducing core symptoms [3,4]. However, functional impairments frequently persist, long-term academic and psychosocial benefits remain debated, and clinical utility is often limited by adverse effects and poor adherence during adolescence [3,5]. These limitations highlight the need for effective nonpharmacological interventions.

Physical exercise has emerged as a promising adjunctive strategy for youth with ADHD [6]. There is evidence suggesting that exercise interventions can improve specific executive function domains, particularly inhibitory control, as well as core symptoms such as inattention [7]. Nevertheless, adherence to high-intensity exercise protocols is often challenging, especially in adolescents, due to monotony and physical discomfort associated with vigorous exertion [8]. Exergaming, which integrates physical exercise with immersive digital environments, has been proposed as a means of combining physiological stimulation with enhanced engagement and motivation [9,10]. Virtual reality (VR)–based exergames in particular allow for the delivery of structured exercise protocols while maintaining high levels of user involvement.

Despite this potential, a key methodological limitation in the current literature is the difficulty of disentangling cognitive and behavioral effects attributable to physiological exertion from those related to the cognitive and motivational features of gaming and VR environments [9]. Many previous studies have relied on passive or nonequivalent control conditions, limiting causal inference regarding the specific contribution of exercise intensity [7].

To address this gap, this randomized clinical trial evaluates the effects of a high-intensity interval training (HIIT)–based VR exergame compared with an active, nonexercise VR control condition in adolescents with ADHD. The primary objective is to determine whether the HIIT-based VR intervention leads to greater improvements in inhibitory control and inattention than VR exposure without physical exertion.

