Several limitations should be acknowledged. The single-blind design introduces the possibility of expectancy effects; however, this risk is partially mitigated by the use of an engaging active control condition matched for novelty and immersion. Notably, expectancy bias may disproportionately affect the parent-reported inattention outcome given that parents are aware of their children’s group assignment. The inclusion of the go/no-go task as a co–primary objective performance measure allows for a complementary assessment that is less susceptible to expectancy effects as it is independent of rater expectations. Furthermore, the 2 study arms differ not only in metabolic load but also in gross motor demand and task experience as the intervention requires full-body movement whereas the control condition involves joystick-only interaction. These differences are inherent to ecologically valid comparisons of this nature and preclude definitive attribution of any observed effects to a single component of the intervention. The 4-week intervention period may be insufficient to induce durable neuroplastic changes or sustained behavioral adaptations as longer intervention durations have been associated with stronger consolidation of executive function gains in meta-analytic studies. Nevertheless, budgetary and logistical constraints limited the feasibility of implementing longer protocols, and the selected intervention length is consistent with the duration most commonly used in studies evaluating HIIT, neuromodulation, and computerized cognitive training for ADHD [27]. Excluding participants currently receiving pharmacological treatment limits generalizability but was necessary to isolate the specific effects of the exercise intervention. Although parent-reported inattention outcomes may be subject to rater bias, this limitation is offset by the inclusion of objective, performance-based measures of inhibitory control, which have demonstrated sensitivity to high-intensity exercise interventions. Finally, while home-based delivery precludes direct supervision, structured remote monitoring provides systematic indexes of adherence and training intensity, thereby ensuring intervention fidelity.

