If the study demonstrates significant improvements in inhibitory control and inattention in the HIIT VR group compared with the nonexercise VR control, these findings will support the clinical efficacy of an HIIT-based VR exergame as a novel, engaging nonpharmacological intervention for adolescents with ADHD. Such results would have important implications for expanding treatment options in a population characterized by limited adherence to existing therapies. Conversely, if no differential effects are observed between groups, this would suggest that immersive VR engagement itself may represent a key therapeutic component, providing valuable insights for the design of future digital and game-based interventions. By evaluating a developmentally appropriate, home-based HIIT VR intervention within a rigorously controlled design, this trial has the potential to advance both the clinical and methodological evidence base for nonpharmacological treatments in ADHD. Results will be disseminated through peer-reviewed publications and scientific conferences regardless of the direction of the findings.

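### The stated 0.80 power reads as a single-outcome figure, but the only efficacy conclusion described rests on both co-primary outcomes; if both are required, its power is about 0.64 to 0.71

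*Protocol article*

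**What the plan says.** The Sample Size section of the protocol article has a single set of inputs: "The sample size calculation assumed a statistical power of 0.80, a significance level of an α value of .05, and a medium effect size of" … The effect size given there is 0.50, attributed to earlier exercise studies in this condition. The section adds 30% attrition and arrives at 98 participants, 49 per arm. It names no outcome and does not mention that there are two.

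The Abstract, Table 1 and the Primary Outcomes section list two primary outcomes: the parent-reported SNAP-IV inattention score and go/no-go commission errors. Three other places join them:

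- The Introduction sets the primary objective as whether the intervention "leads to greater improvements in inhibitory control and inattention than VR exposure without physical exertion".
- The limitations paragraph of the Discussion refers to "The inclusion of the go/no-go task as a co–primary objective performance measure".
- The closing paragraph of the Discussion opens its efficacy conclusion with "If the study demonstrates significant improvements in inhibitory control and inattention in the HIIT VR group compared with the nonexercise VR control".

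The Statistical Methods section sets the threshold ("Statistical significance will be defined as a 2-sided" P value under .05) but gives no rule for combining the two tests. The closing paragraph gives one further reading, for the case where the groups do not differ. It says nothing about a result that is significant on one outcome only.

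**The concern.** A power figure belongs to a decision rule. One effect size, one alpha and one power describe the chance that one test succeeds. The efficacy conclusion as written needs two tests to succeed, and the chance of that is smaller unless the two test statistics are perfectly correlated. This is a type II error matter. It is separate from multiplicity of false positives, and it would remain even if 0.80 per outcome were exactly right.

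What is at stake is how the result is read. With 0.80 power for each test and both effects real, exactly one test is significant with probability 2 × (0.80 − joint power): 2 × (0.80 − 0.640) = 0.32 at correlation 0, and 2 × (0.80 − 0.687) = 0.23 at correlation 0.5. The article offers no reading for that outcome, although it would be common under the plan's own assumptions.

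**Working it through.** **Inputs.** From Sample Size: power 0.80, alpha .05, effect size 0.50 (read here as Cohen d), 30% attrition, 98 in total, 49 per arm. From Statistical Methods: two-sided testing. From Randomization and Blinding: 1:1 allocation. The correlation ρ between the two test statistics is not given, so it is an assumption and is shown as a range.

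**Step 1: the plan's own figure.** For a plain two-sample comparison, n per arm = 2(z₀.₉₇₅ + z₀.₈₀)²/d² = 2(1.960 + 0.842)²/0.25 = 62.8, so 63 (64 with the exact t-test). That is 126 or 128 completers, and 126/0.70 = 180 or 128/0.70 = 183 enrolled. Multiplying by 1.30 instead gives 164 or 167. One-sided testing gives 100 or 102 before attrition and 143 or 146 after. The stated 98 is not reproduced. It can be reached only by dropping a stated input or adding an unstated one, for example an analysis of covariance with a baseline correlation of about 0.68: 62.8 × (1 − 0.68²) = 33.8, so 34 per arm, and 68/0.70 = 97.1, so 98.

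**Step 2: could 0.80 already be the joint figure?** In a plain two-sided two-sample comparison at d = 0.50 (normal approximation), joint power of 0.80 needs 83, 81, 79 or 74 completers per arm at ρ = 0, 0.3, 0.5 or 0.8. That is 238, 232, 226 or 212 enrolled at 30% attrition, more than twice the planned 98. With one effect size and no outcome named, 0.80 is best read as a single-outcome figure.

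**Step 3: joint power if each test has 0.80.** Each statistic is approximately normal with mean 1.960 + 0.842, so joint power = P(Z₁ < 0.842, Z₂ < 0.842) for standard bivariate normal variables with correlation ρ.

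| ρ | Joint power | Points below 0.80 |
|---|---|---|
| 0 | 0.640 | 16.0 |
| 0.3 | 0.666 | 13.4 |
| 0.5 | 0.687 | 11.3 |
| 0.7 | 0.713 | 8.7 |
| 0.9 | 0.750 | 5.0 |
| 1 | 0.800 | 0 |

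**Step 4: the same calculation at the planned numbers.** Two-sided two-sample t-test, d = 0.50. Completers per arm: 49 × 0.70 = 34.3, taken as 34.

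| Per arm | Single test | Joint, ρ = 0 | Joint, ρ = 0.3 | Joint, ρ = 0.5 |
|---|---|---|---|---|
| 49 (no attrition) | 0.688 | 0.473 | 0.513 | 0.542 |
| 34 (30% attrition) | 0.529 | 0.279 | 0.328 | 0.362 |

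**Step 5: separating the two causes.** The fall from 0.80 to 0.53 for a single test has nothing to do with having two outcomes; it is the Step 1 discrepancy. Only the gap in Step 3 is due to the second outcome. Step 4 is also not the planned analysis, which is a mixed model using baseline and follow-up. Its power depends on the baseline-to-follow-up correlation, which the article does not give. If 0.50 is in units of the outcome SD, a comparison of change scores for 0.80 single-outcome power needs 88 completers per arm at a correlation of 0.3, 63 at 0.5 and 38 at 0.7.

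**The case against.** The strongest objection is that the Methods never say both outcomes must be significant. The sentence in the Discussion gives a condition under which efficacy would be supported; logically it is sufficient, not necessary. The word joining the two outcomes in the objective may only list them, and the limitations paragraph describes go/no-go as complementing the parent rating, which fits two outcomes read side by side. If either outcome were enough, joint power would not be the relevant figure. This stands, and it is why the point is conditional on a both-required rule. What remains is that significance on both is the only route to an efficacy conclusion that the article describes, and it agrees with the objective and the co-primary label.

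Three stronger readings are tempting, and the document does not support them:

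- A reader might infer that the trial's real power is 28% to 36% because there are two outcomes. Most of that drop comes from the sample size not following from its inputs, and the figures are for a plain t-test, not the planned model.
- A reader might assume that a parent rating and a computerized task correlate weakly, which would favour the lower end of the range. The article gives no correlation and no source for one.
- A reader might infer that the plan would count a split result as evidence against efficacy. The article ties its negative reading to no difference between groups and leaves a split result open.

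It can also be said that an unseen analysis plan may settle the decision rule. It may, but the power figure and the conclusion are both printed here, and as printed they do not refer to the same event.

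**Conclusion.** The point holds in conditional form. The stated 0.80 reads as the power for one outcome. If the efficacy conclusion needs both co-primary outcomes, its power is below 0.80 at any correlation below 1: 0.64 to 0.71 over assumed correlations of 0 to 0.7, taking 0.80 per test at face value. The part due to two outcomes is 9 to 16 points.

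This rests on three assumptions: that both outcomes are required, which is inferred from the objective, the co-primary label and the closing paragraph; that 0.80 is a single-outcome figure, which is inferred from the single effect size and from Step 2; and the correlation range. The document does not support saying that the protocol formally requires both outcomes, or that having two outcomes alone takes power to about 30%.

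**What to change.** - **Methods.** State the decision rule: both co-primary outcomes must reach two-sided P < .05 for the efficacy conclusion in the Discussion. This rule needs no alpha adjustment.
- **Sample Size.** Say that 0.80 refers to a single outcome. Add the joint power at the planned enrolment and attrition for correlations from 0 to 0.5, computed for the planned model with its assumed baseline correlation stated.
- **Discussion.** Say that under this rule one significant outcome alone does not meet the confirmatory criterion and will be reported as such, and that non-significance on the other outcome is not evidence of no effect.
- **If either outcome is meant to suffice.** Say so and control the type I error, for example with Holm, in place of quoting joint power. Two independent tests at an unadjusted .05 give at least one false positive with probability 1 − 0.95² = 0.0975.

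The cost is a short recalculation and a few sentences, with no change to enrolment. The downside is a less favourable stated power. The Results section reports that no interim analyses have been conducted, so the rule can still be fixed before results are seen.
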